## Abstract

**Background:**

Understanding how and why de-implementation of low-value practices is sustained remains unclear. The Paediatric Research in Emergency Departments International CollaboraTive (PREDICT) Bronchiolitis Knowledge Translation (KT) Study was a cluster randomised controlled trial conducted in 26 Australian and New Zealand hospitals (May-November 2017). Results showed targeted, theory-informed interventions (clinical leads, stakeholder meetings, train-the-trainer workshop, targeted educational package, audit/feedback) were effective at reducing use of five low-value practices for bronchiolitis (salbutamol, glucocorticoids, antibiotics, adrenaline and chest x-ray) by 14.1% in acute care settings. The primary aim of this study is to determine the sustainability (continued receipt of benefits) of these outcomes at intervention hospitals two-years after the removal of study supports. Secondary aims are to determine sustainability at one-year after removal of study support at intervention hospitals; improvements one-and-two years at control hospitals; and explore factors that influence sustainability at intervention hospitals and contribute to improvements at control hospitals.

**Methods:**

A mixed-methods study design. The quantitative component is a retrospective medical record audit of bronchiolitis management within 24 hours of emergency department (ED) presentations at 26 Australian (*n* = 20) and New Zealand (*n* = 6) hospitals, which participated in the PREDICT Bronchiolitis KT Study. Data for a total of 1800 infants from intervention and control sites (up to 150 per site) will be collected to determine if improvements (i.e., no use of all five low-value practices) were sustained two- years (2019) post-trial (primary outcome; composite score); and a further 1800 infants from intervention and control sites will be collected to determine sustained improvements one- year (2018) post-trial (secondary outcome). An a priori definition of sustainability will be used. The qualitative component will consist of semi-structured interviews with three to five key emergency department and paediatric inpatient medical and nursing staff per site (total *n* = 78-130). Factors that may have contributed to sustaining outcomes and/or interventions will be explored and mapped to an established sustainability framework.

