#### Quantitative study

##### Selection of patients with bronchiolitis

A retrospective patient medical record audit will be conducted by designated site study staff at each consenting site, under the supervision of site Principal Investigators. A list of all infants who presented between 1 January 2018 and 31 December 2019 with International Classification of Diseases 9th and 10th revision (ICD-9 or ICD-10) discharge codes for bronchiolitis (Table 2) will be retrospectively identified. To be eligible for inclusion, patients must be: aged less than 1 year (at time of presentation); AND have both an ED and discharge diagnosis of bronchiolitis. There are no patient-level exclusion criteria.

**Table 2 Tab2:** International Classification of Diseases (ICD) codes used for identifying patients

ICD code		Description
ICD–10	J21	Acute bronchiolitis
	J21-0	Acute bronchiolitis due to respiratory syncytial virus
	J21-1	Acute bronchiolitis due to human metapneumovirus
	J21-8	Acute bronchiolitis due to other specified organisms
	J21-9	Acute bronchiolitis, unspecified
ICD-9	466-11	Acute bronchiolitis due to respiratory syncytial virus
	466-19	Acute bronchiolitis due to other infectious organisms

Data for a total of 1800 infants (approximately 150 infants per site) will be collected at 2 years post-trial (2019), to address the primary outcome. Similarly, data from 1800 infants will be collected at one-year post-trial (2018). If a site has less than 150 infant presentations per year, 100% of eligible infants will be selected. If a site has more than 150 infant presentations per year, a random sample of 150 infants per year will be selected by an independent statistician using computer software.

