#### Sample size

The sample size for this medical record audit will depend on the number of participating hospitals and will be recalculated upon completion of the hospital recruitment stage. Based on our previous study [4], assuming an Intra-cluster Correlation Coefficient of 0.11, an expected proportion of no use of all five low-value practices) of 85% (based on results of the PREDICT Bronchiolitis KT Study) [4] and a Coefficient of Variation of cluster sizes of 0.16 [4], a total sample size of 1800 (obtained from 12 intervention hospitals (clusters) with an average size of 150 infants) will achieve a confidence interval (CI) half-width of 7% (95%CI: 78 to 92%). An equivalent number of infants, i.e. 1800 in total, will also be obtained from ~ 12 control hospitals (clusters) with an average size of 150 infants.

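### The abstract gives 1800 infants per year for both groups together, the sample-size section gives 1800 per group, and the latter uses the 150-per-site maximum as an average

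*Protocol article*

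**What the plan says.** The sample for the record audit is described in three places.

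- **Abstract, Methods.** For 2019: "Data for a total of 1800 infants from intervention and control sites (up to 150 per site) will be collected". For 2018: "a further 1800 infants from intervention and control sites will be collected". Both sentences name both groups, so the total over two years is 3600.
- **Selection of patients with bronchiolitis.** "Data for a total of 1800 infants (approximately 150 infants per site) will be collected at 2 years post-trial (2019", to address the primary outcome, and similarly for 2018. No group is named. The sampling rule follows: "If a site has less than 150 infant presentations per year, 100% of eligible infants will be selected", and at larger sites "a random sample of 150 infants per year will be selected".
- **Sample size (quantitative).** The precision calculation rests on "a total sample size of 1800 (obtained from 12 intervention hospitals (clusters) with an average size of 150 infants". It then adds: "An equivalent number of infants, i.e. 1800 in total, will also be obtained from ~ 12 control hospitals". The other inputs are an expected proportion of 85%, an intra-cluster correlation of 0.11 and a CV of cluster sizes of 0.16. The stated result is a 95% confidence interval half-width of 7% (78 to 92%). The section also says the sample size will be recalculated once hospital recruitment is complete.

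**The concern.** Two statements conflict with others in the same article.

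First, 1800 is the yearly total for both groups in the abstract and the yearly total for one group in the Sample size section. A reader cannot tell whether the audit covers 3600 or 7200 records, and so cannot later judge whether the target was met. The Selection section could settle this but leaves the group unnamed.

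Second, the sampling rule makes 150 the most a site can contribute in a year, while the calculation treats 150 as the average and also assumes that cluster sizes vary. Both cannot hold, and the effect is to overstate the number of infants that 12 hospitals can supply.

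**Working it through.** **Inputs.** From the Sample size section: p = 0.85, ICC = 0.11, CV = 0.16, k = 12 intervention hospitals, average m = 150. From the abstract and the Selection section: a maximum of 150 per site per year. From the Background and the Setting section: 13 hospitals per group in the parent trial, all 26 invited.

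**1. Reproducing the stated 7%.**

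Design effect for unequal clusters: DE = 1 + ((CV² + 1) × m − 1) × ICC.

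Half-width = 1.96 × √(p(1 − p) × DE / (k × m)).

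- DE = 1 + (1.0256 × 150 − 1) × 0.11 = 17.81.
- Half-width = 1.96 × √(0.1275 × 17.81 / 1800) = 6.96%.

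The plan's 7% is reproduced with 1800 infants in the intervention group alone. If 1800 were one sample spread over 24 hospitals of both groups (75 each), the same formula gives DE = 9.35 and a half-width of 5.0%, which is not the stated figure.

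**2. The two totals.**

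| Reading | Per year | 2018 and 2019 |
|---|---|---|
| Abstract: both groups together | 1800 | 3600 |
| Sample size section: per group, 12 + 12 hospitals | 1800 + 1800 = 3600 | 7200 |

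Ceilings under the cap are 12 × 150 = 1800, 13 × 150 = 1950, 24 × 150 = 3600 and 26 × 150 = 3900. The abstract's 1800 would need only 1800/26 = 69 to 1800/24 = 75 infants per site.

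**3. Cap against average.** If no site exceeds 150 and the mean is 150, every site has exactly 150 and the CV is 0. To find the largest total compatible with CV = 0.16, let s of k hospitals fall short of 150 by the same number d, with the rest at the cap, and write f = s/k. Then

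- mean = 150 − f × d;
- SD = d × √(f(1 − f));
- setting SD = 0.16 × mean gives d = 24 / (√(f(1 − f)) + 0.16f).

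For a given total shortfall the CV is largest when one site carries all of it, so s = 1 gives the highest total.

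| Hospitals | Sites below cap | d | Total | Mean |
|---|---|---|---|---|
| 12 | 1 | 82.8 | 1800 − 83 = 1717 | 143 |
| 12 | 3 | 50.7 | 1800 − 152 = 1648 | 137 |
| 12 | 6 | 41.4 | 1800 − 248 = 1552 | 129 |
| 13 | 1 | 86.1 | 1950 − 86 = 1864 | 143 |
| 13 | 2 | 62.3 | 1950 − 125 = 1825 | 140 |
| 13 | 3 | 52.4 | 1950 − 157 = 1793 | 138 |

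With the n − 1 form of the SD, the first row becomes 1720. So 12 hospitals give at most about 1720. With 13 hospitals, 1800 needs an average of 1800/13 = 138.5, which in this layout is met with one or two sites below the cap and just missed with three.

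**4. Effect on precision**, same formula, CV = 0.16, 12 intervention hospitals:

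| Average per hospital | Infants | DE | Half-width |
|---|---|---|---|
| 150 | 1800 | 17.81 | 6.96% |
| 143 | 1717 | 17.03 | 6.97% |
| 125 | 1500 | 14.99 | 7.00% |
| 75 | 900 | 9.35 | 7.13% |

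The row at 125 is an illustrative assumption: the parent trial enrolled 3240 infants in 26 hospitals, 3240/26 ≈ 125. That count covers May to November, whereas this audit covers full calendar years.

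**The case against.** The strongest reply is that little depends on the discrepancy in practice. The per-site rule (all infants below 150, a random 150 above) is the same whichever way 1800 is read, and nothing tells a site to take 75 or to stop at 1800 overall. The Selection section ties its 1800 to the primary outcome, which is defined in intervention hospitals, and at about 150 per site it implies 12 sites. It therefore fits the Sample size section, which leaves the abstract as the outlier. A recalculation is already planned. All of this stands, and it limits the harm. It does not remove the conflict: the abstract names both groups explicitly, and the promise to recalculate does not say whether 1800 is a group total or a study total, nor that the average will be brought below the cap.

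Three stronger readings are tempting and are not supported.

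- A reader might infer that 1800 in all at 150 per site means 6 hospitals per group, with a half-width of 9.8%. The plan describes no such design: it invites 26 hospitals and plans 12 and about 12.
- A reader might set a half-width of 8.0% (t quantile, 11 degrees of freedom, 75 per site) against the plan's 7%. The plan used the normal quantile. On the t basis its own 12 × 150 gives 7.8%, so the like-for-like change is again small.
- A reader might call 1800 barely reachable in general. That applies only to the per-group figure with 12 hospitals. As the abstract words it, for both groups together, 1800 is less than half or about half of what the cap allows.

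**Conclusion.** The point holds in two limited parts. The abstract's sample size is half that of the Sample size section (1800 against 3600 per year; 3600 against 7200 over both years, with 12 hospitals per group). The derivation supports the per-group figure, so the abstract should change. Independently, an average of 150, a maximum of 150 and a CV of 0.16 are incompatible: 12 hospitals can supply at most about 1720 infants under the last two, and 13 reach 1800 only if few sites fall below the cap. The 1720 bound is the most favourable arrangement; the totals for other numbers of small sites assume equal shortfalls.

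The consequence is a misstated sample size and an overstated expectation of what the hospitals will supply. The primary estimate is not threatened. With about 12 intervention hospitals the half-width stays between 6.96% and 7.13%, because the number of hospitals governs precision far more than the number of infants in each.

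**What to change.** - **Abstract and Selection of patients:** state that the target is per group per year and name the group to which 1800 refers.
- **All three places:** describe 150 as the maximum per hospital per year, with a ceiling of 1800 per group per year for 12 hospitals and 1950 for 13.
- **Sample size section, at the planned recalculation:** replace the average of 150 with an expected average below 150 that is consistent with both the cap and the CV used, and restate the expected total and half-width. If the parent trial's average of about 125 is used, label it an indicative assumption because of its May to November window.

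The cost is wording in three places and one short recalculation. The per-site sampling rule does not change. The stated number of infants becomes somewhat smaller and the half-width stays at about 7%.

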**Discussion:**

This study will improve our understanding of the sustainability of evidence-based bronchiolitis management in infants. Results will also advance implementation science research by informing future de-implementation strategies to reduce low-value practices and sustain practice change in paediatric acute care.

**Trial registration:**

Australian and New Zealand Clinical Trials Registry No: ACTRN12621001287820.

Contributions to the literature
This will be one of the few studies examining sustainability (continued receipt of benefits) and sustainment (continued use) of an intervention that improved evidence-based practices in acute care settings.Findings will contribute knowledge of the factors that improve the sustainability of evidence-based management of infants with bronchiolitis.Understanding effective sustained implementation strategies will inform future efforts to improve practice in acute care settings as well as future implementation research.

## Background

In infants less than 1 year of age, the most common lower respiratory tract infection is bronchiolitis [1]. Bronchiolitis is caused by a viral infection, most frequently by respiratory syncytial virus and can be life-threating [2, 3]. In Australia and New Zealand, bronchiolitis is the leading cause of hospital admissions in infants under 6 months of age [2, 4, 5] accounting for 56% of Australian hospital admissions in infants less than 12 months of age, 7-9% of New Zealand hospital admissions in children 0 to 14 years of age [5–7], with infants from indigenous and deprived populations being most at risk [8].

Recommended management of bronchiolitis is well defined, comprising of supportive practices such as respiratory and hydration support [2, 3, 9]. There is strong evidence that five therapies and management processes, namely salbutamol, glucocorticoids, antibiotics, adrenaline and chest x-rays (CXRs) are ineffective or ‘low value’ and should not be used in the management of infants with bronchiolitis [1, 5, 10, 11]. Current international clinical practice guidelines, including the 2016 evidence-based guideline from Australia and New Zealand (Australasian Bronchiolitis Guideline) [1, 5] recommend against their use. Yet, variations in practice persist. An Australasian retrospective audit conducted at seven hospitals found that in 3856 infants who presented with bronchiolitis, 27-48% received at least one of the five low-value practices [12]. These results are consistent with the literature [4, 13], showing that even when evidence reveals no benefits, abandoning (i.e. de-implementing) low-value practices is often harder than implementing new practices [14–16]. In response to the variations in practice, we undertook the Paediatric Research in Emergency Departments International CollaboraTive (PREDICT) Bronchiolitis Knowledge Translation (KT) Study to improve bronchiolitis care. It demonstrated that use of targeted, theory-informed interventions significantly improved bronchiolitis care by de-implementing these five low-value practices by 14.1% (adjusted risk difference, 95% CI, 6.5-21.7%; *P* < .001) [4]. The focus of this current study is to determine if the change has been sustained (Fig. 1).

**Fig. 1 Fig1:**
[figure not shown]
Timeline from PREDICT KT Study to the PREDICT KT Sustainability Study

### Sustainability: definition and overview of research

Sustainability studies are rare, with the few undertaken reporting poor long-term (sustained) compliance [17, 18]. This area of research is complicated by no clear or consistent definition of sustainability [19, 20]. Common elements of sustainability have been identified, namely, continued capacity to deliver the intervention, continued provision of the implementation intervention, and ongoing clinical benefit from the intervention [21]. Additionally, there is debate about distinguishing between *sustainability* and *sustainment* [22]. For our purposes, we define sustainability as the degree to which an evidence-based innovation, after external support has ceased, can deliver its benefits as intended over a prolonged period of time i.e. sustained benefits [17, 23]. We define sustainment as the continued use of an implementation intervention i.e. its sustained use [17, 23].

To date, measurement of the ongoing effect of implementation research largely reports success by the ‘clinical outcomes’ that the intervention was designed to change (i.e. sustainability of improved clinical care) [20]. Often there is insufficient reporting on and evaluation of continuation of the process or implementation of the evidence-based intervention (i.e. sustainment) that was used to bring about the change (i.e. sustainment of education delivery or use of clinical champions etc) [18, 20]. Yet systematic reviews assessing the sustainability of effective behaviour change studies with multiple behaviour change components found 60% maintained implementation of only one component of the proven intervention [19, 24, 25]. Thus the measurement of both sustainability and sustainment are important for the long-term understanding of implementation interventions [26]. For the purpose of this study, we define sustainability as the sustained benefits, i.e. the continued clinician behaviour change (no use of the five low-value bronchiolitis practices) [27]. We define sustainment as the continued use of the targeted theory-informed bronchiolitis implementation strategy [23, 27].

### Sustainability frameworks

A wide variety of terms, (i.e. routinisation, durability or institutionalisation) have previously been used when discussing sustainability [28]. However, these terms are rarely operationalised or defined conceptually [28]. Therefore, understanding factors that contribute to sustained interventions is vital. The use of sustainability frameworks can help determine the causal factors which lead to the success or failure of an intervention allowing for future studies to adopt better strategies [29, 30]. Yet the use of sustainability frameworks in research is lacking [31]. Whilst various frameworks have been identified as relevant for sustainability, few have been tested to determine if they are good predictors of sustainability [28, 31]. Furthermore, few frameworks are designed specifically for acute care settings and there is no consensus for which framework is most relevant [30, 31]. Therefore there is a need to test these frameworks to determine applicability in specific settings [28].

#### The PREDICT Bronchiolitis KT Study

The ‘Knowledge Translation (KT) in Australasian Paediatric Acute Care Settings Study’ (PREDICT Bronchiolitis KT study) (ACTRN12616001567415) was a multi-centre, cluster randomised controlled trial conducted in 26 Australian and New Zealand hospital Emergency Departments (EDs) and paediatric inpatient areas during the 2017 Southern Hemisphere bronchiolitis season (1st May to 30th November 2017), involving 3240 infants [4]. Of the 26 hospitals, 13 were randomised to the intervention group and 13 to the control group with all hospitals completing the trial. The intervention group received targeted, theory-informed interventions developed to address factors identified as influencing bronchiolitis management in Australia and New Zealand [32]. Interventions consisted of: identification of stakeholder meetings; clinical leads; Train-the-trainer workshop; educational materials with scripted, targeted messaging; other educational material consisting of a clinician video demonstrating how to talk with families about bronchiolitis, promotional materials, evidence fact sheets; and finally monthly audit and feedback (Table 1) [4, 33]. Both intervention and control group hospitals received printed and electronic copies of the Australasian Bronchiolitis Guideline.

**Table 1 Tab1:** Implementation Strategy Components used in the PREDICT Bronchiolitis KT Study [4, 33]

Intervention Components	Intervention Hospitals	Control Hospitals Post Trial^a^
Clinical leads	Four clinical leads for the duration of the study, included a medical and a nursing lead from each emergency department and inpatient paediatric areas. Key tasks included attending a 1-day train-the-trainer workshop, spearheading educational intervention and other educational materials delivery to all staff, supervising monthly audit completion and delivery of feedback, and management of study requirements.	Encouraged to allocate a medical and nursing lead, but no further guidance provided.
Stakeholder Meetings	Study team presented the Australasian Bronchiolitis Guideline to clinical leads, discussed local and international bronchiolitis management variations, reviewed results of the local audit, and discussed any local anticipated barriers, with the aim to gain site buy-in.	Nil.
Train-the- trainer workshop	1-day workshop for clinical leads: discussed Australasian Bronchiolitis Guideline and evidence supporting recommendations, qualitative study identifying the facilitators and barriers of bronchiolitis management, implementation, and the development of interventions. Clinical leads received demonstrations on how to deliver educational interventions to their staff, outlines of study data timelines and requirements, and enabled planning time for clinical leads.	One-day workshop providing bronchiolitis intervention materials, with up to four clinical leads (medical and nursing) invited to attend. Discussion on what the aims of education materials were. Individual hospital data from the cluster RCT was presented (2014-2017). Feedback in relation to similar hospitals.
Educational intervention delivery	Key findings from qualitative study were presented in a PowerPoint with scripted messages stating use of behaviour change techniques most likely to effect change. Clinical Leads oversaw education delivery to medical and nursing staff using PowerPoint presentation. Within first month, aimed to educate 80% of staff and to ensure all staff educated ongoing education provided throughout duration of study.	PowerPoint presentation which was the same as presentation provided to the intervention hospitals.
Use of other educational materials	Clinical leads locally delivered promotional materials, evidence factsheets, clinician training video, and parent/caregiver information.	Education materials that were provided to the intervention hospitals.
Audit and feedback	Monthly audits of the first 20 bronchiolitis presentations, with report providing comparison between individual hospital results and top-performing site. Clinical leads disseminated report to their staff in written and verbal format; action planning with target setting encouraged.	Audit form and own hospital results from trial (4 years of data).
Ongoing facilitation	Weekly contact between clinical leads and study leads. Opportunities to ask questions via email.	Nil.

^a^delivered at trial completion in November 2018

Findings of the PREDICT Bronchiolitis KT Study demonstrated that, when compared with control hospitals, intervention hospitals significantly improved adherence in management of bronchiolitis during the acute care period (first 24 hours of hospital presentation) for the five key low-value practices as per Australasian Bronchiolitis Guideline recommendations (14.1% adjusted risk difference, 95% CI, 6.5-21.7%; *P* < .001) [4, 34]. Specifically, during the acute care period (first 24 hours of hospital presentation), adherence to the Australasian Bronchiolitis Guideline recommendations with no use of salbutamol, glucocorticoids, antibiotics, adrenaline and CXRs, was 85% (95% CI, 82.6-89.7%) in the intervention group hospitals compared with 73% (95% CI, 65.3-78.8%) in the control group hospitals [4, 34]. At trial completion (November 2018), up to four nurses and doctors from each of the 13 control hospitals attended a 1 day workshop where they were given training and provided with intervention materials (Table 1). However, no on-going facilitation was provided.

